### Interim analyses {21b}

The study’s Data and Safety Monitoring Board (DSMB), whose purpose is to protect the safety of participants and promote the scientific integrity of the study, will include five members. The DSMB will monitor study participant accrual, protocol adherence, data quality, site performance, SAEs and other subject safety issues and will review formal interim statistical analyses of treatment efficacy. The EDC will send reports relating to DSMB members prior to each meeting. The EDC will attend DSMB meetings; each meeting will have summary recommendations that will be provided to the principal investigators who will be responsible for responding to all recommendations. The EDC will distribute the final signed recommendation within 3 business days to the investigators, DSMB members, and the federal funding agency and will post the final signed recommendations to the EDC Document Library.

The DSMB had its inaugural pre-launch meeting on June 17, 2022, and an additional meeting was convened on July 29, 2022, to address outstanding concerns prior to study launch. The DSMB will hold two planned meetings to review formal interim analyses to examine treatment efficacy and patient safety. The first formal efficacy analysis will occur prior to the intervention switch (i.e., crossover). This analysis will test the primary hypothesis by using the model described for the analysis of the primary outcome but without a period effect term. In the second intervention phase, a formal interim efficacy analysis will occur after the seasonal peak of STEC incidence. Early stopping of the trial will be considered if efficacy has been established. One-sided Haybittle–Peto boundaries will be used for efficacy monitoring. The trial may be stopped for harm and such analyses will be performed as part of our interim analysis. The DSMB will review accumulating AE data and weigh the potential risks and benefits at each meeting. If there is a perceived increase in risk of AEs with little indication of benefit, the DSMB has the ability to recommend stopping the trial. In addition, they will meet every 12 months to review the protocol, study procedures, monitoring, participant safety, enrollment, and loss to follow-up.

This study may be suspended or prematurely terminated if there is sufficient reasonable cause at an ad hoc DSMB meeting. The following events will trigger a notification to the DSMB chair to determine whether an ad hoc DSMB meeting is warranted to review AEs and to make recommendations to the principal investigators:Mortality frequency > 1% of participantsRRT frequency > 15% of participantsIntubation frequency > 5% of participants (minimum duration > 24 h)

When considering such AE data, the DSMB will be encouraged to consider the number of participants enrolled to date.

Written notification, documenting the reason for study suspension or termination, will be provided by the EDC to investigators, funding agencies, the central IRB, and local REBs. The notification will include the reason(s) for the termination or suspension. The study may resume once the identified concerns are addressed to the satisfaction of the sponsor, IRB/REBs, and the DSMB.

### Methods for additional analyses (e.g., subgroup analyses) {20b}

For additional insight, we will perform a “confirmatory” analysis restricted to patients with high-risk STEC, defined as meeting one of the following criteria:Evidence of Stx2 infectionEvidence of O157, O103, O104, O111, O113, O121, or O145 infectionBloody diarrhea and no toxin or typing availableEarly HUS and no toxin or typing available

This is the population that would be “ideal” for the trial. However, the identification of this population prior to initiation of treatment is not feasible with current technology and workflow.

The primary outcome will be analyzed across predefined subgroups to look for a differential treatment effect. Subgroups will be based on age (0 to < 5.0, 5.0 to < 10.0, and ≥ 10.0 years), sex, duration of diarrhea prior to pathway initiation (< 96 and ≥ 96 h), and baseline hematocrit (< 40% and ≥ 40%). A subgroup effect will be considered significant if the interaction between subgroup and treatment (added to the same model as used for the primary analysis) is significant at a Bonferroni-corrected level. Exploratory outcomes will be analyzed in the same way as the primary and secondary outcomes with no adjustment for multiple comparisons. When these results are reported, they will be identified as exploratory.

Safety analyses: frequencies of SAEs will be compared between subjects allocated to hyperhydration vs. those allocated to conservative fluid management. The occurrence of any SAE will be considered as a dichotomous outcome. The start date, stop date, severity, relationship, expectedness, outcome, and duration of SAEs will be reported and treatment-associated SAEs will be presented in a table or listing.

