### Hyperhydration

Data related to all intravenous fluids administered will be extracted from the medical record. For the calculation of pathway adherence, the intravenous fluid administration period begins (i.e., time of study initiation) at the:Time of hospital admission plus 2 h (for participants asked to come to the hospital)* ORTime the participant met eligibility criteria plus 2 h (for participants already in hospital)* ORActual time of initiation of intravenous fluid administration if occurs before the additional 2-h period has lapsed

*Some participants will be admitted into the hospital before eligibility, and some will become eligible before admission (i.e., positive STEC result in child who is at home). The later of the time points between options (1) and (2) will be used to determine the timing of study initiation if (3) does not apply.

The intravenous fluid administration period ends (i.e., time of study end for pathway adherence determination) when any fluid protocol termination criteria are met (i.e., weight/hematocrit targets, complication ensues, end-of fluid protocol criteria) or after 48 h of fluid administration—whichever happens first. The targeted volume of fluid is defined by the administration of ≥ 175% of maintenance fluids calculated according to the Holliday–Segar formula for the duration of time the participant was in the volume expansion phase of the protocol [38]. Thus, adherence is defined as the administration of fluids in excess of: 100% maintenance fluids × 1.75 × number of hours the participant was in the volume expansion phase of the protocol. Boluses will be included in the quantification of total fluids. Exact monitoring and recording of oral fluid intake are logistically prohibitive and will not be included in the fluid calculation.

The management of patients who receive < 175% of maintenance intravenous fluids in the hyperhydration arm will be classified as nonadherent. However, all patients will be included in the intent-to-treat (ITT) analyses regardless of the volume of fluids administered; secondary analyses will include a per protocol adherence analysis.

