### Conservative fluid management

Outpatient/emergency department: All these participants will be considered adherent.

Inpatient: Adherence is defined by the administration of < 110% of maintenance fluids calculated according to the Holliday–Segar formula [38] during the period of time when the participant was in the fluid administration phase of the pathway (defined as per hyperhydration). Thus, adherence to the conservative fluid management pathway is defined as the administration of fluids at or below the following threshold: 100% maintenance fluids × 1.1 × number of hours the participant was in the fluid administration phase. Boluses will be included in the quantification of total fluids. Exact monitoring and recording of oral fluid intake are logistically prohibitive and will not be included in the fluid calculation.

The management of patients who receive > 110% of maintenance intravenous fluids will be classified as nonadherent. However, all patients will be included in ITT analyses regardless of the volume of fluids administered; secondary analyses will include a per protocol adherence analysis.

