**Fig. 5 Fig5:**
[figure not shown]
Approach to optimize the enrollment of high-risk STEC infected participants

For all discharged and outpatients, the child will be asked to go to the ED (if required for the hyperhydration arm) for screening (i.e., baseline laboratory testing) and treatment per the institution allocated pathway. If in the conservative fluid management arm, at the discretion of the responsible physician, the child may be managed as an outpatient and consented for research electronically.

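### The diarrhea-duration subgroup is measured to pathway initiation, a moment that depends on the arm for children identified at home and is not defined for conservative outpatients

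*Protocol article*

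**What the plan says.** The protocol article's section on additional analyses {20b} splits the primary outcome by "duration of diarrhea prior to pathway initiation", below 96 h against 96 h or more. It judges each subgroup by whether the subgroup-by-treatment interaction, added to the primary model, "is significant at a Bonferroni-corrected level". That section does not define pathway initiation.

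The one operational start time stands under the Hyperhydration adherence heading. A child called in starts at "Time of hospital admission plus 2 h (for participants asked to come to the hospital"). A child already in hospital starts 2 h after meeting eligibility. Actual start of intravenous fluid replaces either if it comes earlier. Otherwise, "The later of the time points between options (1) and (2) will be used to determine the timing of study initiation".

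The Conservative fluid management adherence section carries this definition over to inpatients. For the rest it says only "Outpatient/emergency department: All these participants will be considered adherent", with no start time.

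Three places show that the route to the start differs by arm:
- Note 1 to the schedule of activities (Table 2) allows a discharged child to be called back at a hyperhydration site.
- The text after Fig. 5 sends such children to the emergency department where hyperhydration requires it, whereas under conservative management "the child may be managed as an outpatient and consented for research electronically".
- The Discussion says the conservative pathway can begin while the family is at home.

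**The concern.** A subgroup variable should take the same value for a given child whichever arm the site is in. Here it need not. A child at home whose result arrives shortly before 96 h of diarrhea can be counted as early if the pathway starts at home, and as late if it starts only after recall and admission. The two arms within a duration stratum would then be selected by slightly different rules.

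Conservative outpatients raise a second problem. Subgroup analyses use the intention-to-treat population ({20c}), so these children need a value, and the only written clock gives them none. If that clock were started when an outpatient is later admitted, the child would be classed by getting worse, which is a consequence of the disease course the trial is studying.

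This subgroup carries weight because the Background ties benefit to early fluid: it cites a cohort in which children without intravenous fluids in the first 4 days (96 h) of diarrhea fared worse. Readers will look here for early-versus-late evidence.

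**Working it through.** **The plan's own figure.** The article states 90% power (26 sites, 1040 children, 10% vs 5%, ICC 0.106). With 520 per arm and effective n = 520/(1 − 0.106) = 581.7:
- SE under the null = √(2 × 0.075 × 0.925/581.7) = 0.01544
- SE under the alternative = √((0.10 × 0.90 + 0.05 × 0.95)/581.7) = 0.01538
- Power = Φ[(0.05 − 1.96 × 0.01544)/0.01538] = Φ(1.28) = 90.0%

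The figure reproduces, and nothing in this point enters it.

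**Who is affected.**

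| Child | Hyperhydration | Conservative |
|---|---|---|
| Already in hospital | Eligibility + 2 h, or earlier IV start | Same rule if an inpatient |
| At home or discharged when identified | Admission + 2 h after recall, or earlier IV start | May start at home; no time stated |

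Only the second row depends on the arm.

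**How many would change subgroup.** The documents give neither the distribution of diarrhea duration nor the recall delay, so these inputs are assumptions:
- Duration at notification is lognormal, median m = 72 to 96 h, log SD 0.4.
- Recall and admission take 4 to 12 h. Adding the 2 h in the rule gives a shift s = 6 to 14 h.
- At-home conservative children start at notification with no delay.
- 41% are at home: the complement of the 59% directly hospitalized in the earlier multicenter cohort cited in the Background (1 − 0.59).

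Share of called-back children crossing the cut = Φ[ln(96/m)/0.4] − Φ[ln((96 − s)/m)/0.4].
- Lowest, m = 72, s = 6: Φ(0.719) − Φ(0.558) = 0.764 − 0.711 = 5.3%; × 0.41 = 2.2% of the arm.
- Highest, m = 84, s = 14: Φ(0.334) − Φ(−0.060) = 0.631 − 0.476 = 15.5%; × 0.41 = 6.4% of the arm.

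Of 520 children, that is about 11 to 33. If duration were instead uniform over 0 to 240 h (the eligibility limit of 10 days), the share is s/240 = 2.5% to 5.8%; × 0.41 = 1.0% to 2.4% of the arm.

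**Effect on the subgroup result when treatment does nothing.** Assume duration is normal (mean 84 h, SD 36 h, limited to 6–239 h), risk is 10% at 84 h, and the log-odds slope is ±0.01 per hour. Shift every hyperhydration child, which overstates the problem. Integrating the risk over each stratum in each arm gives:
- 6 h shift: within-stratum odds ratios 0.96 to 1.04.
- 24 h shift: 0.86 to 1.17.
- Ratio of the two strata's odds ratios, shifts of 2 to 24 h: 1.00 to 1.02. A simulation of the same scenario gave 0.99 to 1.00.

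Both strata move together, so the interaction hardly changes.

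**Outpatients admitted later.** In the same earlier cohort, 17% of those managed as outpatients returned with HUS. If both rates held in the conservative arm, 0.41 × 0.17 = 7% would be outpatients later admitted with HUS. The Background puts HUS at a median of about 7.5 days (180 h) from onset of diarrhea. A clock started at that admission would therefore place most of them at 96 h or later. This is one possible reading of the rule, not a stated one.

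**The case against.** The strongest reply is that two terms are being joined. The subgroup uses pathway initiation; the written clock is for adherence, and nothing says one supplies the other. The Discussion speaks of the conservative protocol being initiated at home, so outpatients do have an initiation event. Only its timestamp is missing, and a condensed article may leave that to the analysis plan or the manual of operations. This stands as far as it goes, and the missing timestamp alone would be no finding. It does not remove the arm dependence: on the ordinary meaning of initiation too, a child at home starts later where recall and admission come first. The article also refers, for MAKE30, to a time 0 already defined, as if one existed for everyone.

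Four stronger readings are tempting, and the documents do not support them.
- **That a time after allocation is itself the fault.** Site allocation was revealed on May 6, 2022 and recruitment began on September 19, 2022, so every patient-level time follows allocation, including eligibility. Only dependence on the arm matters.
- **That the shift affects the whole hyperhydration arm.** The 2 h added for children in hospital applies to conservative inpatients too and cancels.
- **That 41% of the conservative arm has no start time.** That share comes from an earlier cohort with no pathway in place; here admission is recommended when microangiopathy is present.
- **That the interaction test is badly biased.** The check above shows it is not, from this shift alone.

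Zero delay for at-home conservative children is also generous to the concern, because that pathway includes a protocolized baseline evaluation. Any delay there narrows the gap between arms.

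**Conclusion.** The point holds in a limited form. As written, the duration subgroup depends on the arm for children identified at home or after discharge, and the article's only operational clock leaves conservative outpatients without a value. Under the assumed delays, durations and 41% at home, about 2% to 6% of the hyperhydration arm would change stratum, with little effect on the interaction. How conservative outpatients are to be classified is the larger uncertainty. Its size cannot be fixed from the documents, and the analysis plan, which is not shown, may settle it. One secondary subgroup analysis is affected. A reader might infer from the time 0 cross-reference that the primary result is also compromised; nothing here shows that, and the primary model, sample size and power are unaffected. This is a minor improvement, worth making because it is cheap.

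**What to change.** In the additional-analyses section {20b}, define the subgroup as duration of diarrhea at the time the child met eligibility, derived identically in both arms whether or not the child comes to hospital. Tie that time to the qualifying stool result or presumptive HUS diagnosis, not to later screening bloods, because the text after Fig. 5 lets those bloods wait for an emergency visit in the hyperhydration arm. Arm-dependent reclassification from recall is then zero by construction, and outpatients get a value.

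The change is one phrase. Onset of diarrhea is already needed for the 10-day exclusion, and eligibility time already feeds the adherence clock. The team should confirm that it is also captured for conservative outpatients, since the schedule of activities is not visible here. The cost is interpretive: the subgroup then describes time to eligibility, not time to treatment start, which is slightly further from the early-fluid rationale. No treatment rule and no power figure changes.

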### Methods in analysis to handle protocol non-adherence and any statistical methods to handle missing data {20c}

The primary analysis will be performed using the ITT population, consisting of all participants who are enrolled, included within the study arm corresponding to the treatment assigned to the site during that study period. The ITT population will also be the population used in all secondary outcome, safety, and subgroup analyses. A per-protocol analysis will be conducted to gain additional insight, but the results will not replace the results of the ITT analysis. The per-protocol analysis dataset will consist of the subset of the ITT population who are confirmed eligible and are classified as protocol “adherent.”

Per the ITT principle, subjects who withdraw from the study or are lost to follow-up will have all available data used in the analysis. Subjects who are missing data for a particular outcome will not be included in analysis of that outcome. If a substantial number of subjects are withdrawn or lost to follow-up, baseline characteristics and available information on hospital course will be reviewed and compared to subjects not withdrawn or lost, to assess empirically if these subjects differ from those remaining in the study for the scheduled treatment and follow-up time. However, we expect very little missing data for the primary outcome.

### Plans to give access to the full protocol, participant level-data, and statistical code {31c}

The study’s protocol will be published in a peer-reviewed journal, and it will be submitted, alongside the manuscript reporting the main results of the trial, following trial completion. The study will also comply with the NIH’s Data Management and Sharing Policy. In addition, this trial has been registered at ClinicalTrials.gov (NCT05219110), and the record will be updated in accordance with their policies. The statistical code used to analyze study data will be shared upon reasonable request. The data and supporting information will be made available and will remain open access in the public domain within 3 years following completion of the study protocol by the last enrolled participant.

## Oversight and monitoring

### Composition of the coordinating center and trial steering committee {5d}

The organization of the trial leverages the infrastructure, expertise, and leadership of the Pediatric Emergency Care Applied Research Network (PECARN) [48] and Pediatric Emergency Research Canada (PERC) [49] research networks. The organizations have reviewed and provided extensive feedback that has been integrated into the final protocol which they have approved. The PECARN EDC located at the University of Utah will serve as the study’s data coordinating center and will serve as the central organizing site and is responsible for the preparation and maintenance of study training documents. The EDC will liaise with the Central IRB and the DSMB and will conduct all statistical analyses. The EDC is a unit that operates independently from all participating study sites.

The Executive Committee, composed of the study co-PIs (SF, DS, PT), the PI of the EDC (TCC), and co-investigators (SG, SG, AP), will serve as the overall governing body and will be tasked with assuring that major milestones, timelines, and enrollment targets are met. The Executive Committee will work closely with the NIAID Program Officer, EDC, and DSMB in the oversight of the trial.

A separate Steering Committee, composed of the Executive Committee members and the leaders of the PECARN, PERC, and the PEMCRC networks and a pediatric bioethicist (BW), will meet every 6 months. This committee will provide high-level oversight and guidance regarding ethical and logistical considerations, study conduct, and manuscript preparation.

### Composition of the data monitoring committee, its role, and reporting structure {21a}

Safety oversight will be under the direction of the DSMB which is composed of individuals with expertise in pediatric emergency medicine, pediatric intensive care, pediatric nephrology, and biostatistics. Members of the DSMB are independent from study conduct and free of conflict of interest. The DMSB is operating under the rules of an approved charter that was approved at the initial DSMB meeting. Each data element that the DSMB requires to perform its duties has been clearly defined and these will be provided to them by the EDC. The DSMB has provided its input to the study PIs, sponsor, and other regulatory agencies, as appropriate. The funder, represented by an NIAID program officer and medical monitor will be invited to attend open sessions of the DSMB meetings as a consultative non-voting member, and they will receive copies of the minutes and the charter.

### Adverse event reporting and harms {22}

Study research teams will monitor for the occurrence of AEs throughout the study period. AEs may be reported by the subject or caregivers, discovered by investigator questioning, or detected by the clinical care team through physical examination, laboratory test, or other means. The study period is defined as the initiation of treatment (Day 0) through Day 30 (± 7 days). AEs will be recorded on the AE case report form. The nature of each experience, date and time of onset, course, outcome, severity, and relationship to treatment will be established.

Summaries of event rates, intensity, and relationship to study allocation of individual SAEs will be presented by System Organ Class and Preferred Term (MedDRA). MedDRA is a multilingual standardized international medical terminology dictionary used for regulatory communication and evaluation of data pertaining to medicinal products for human use. AE severity will be assessed by the site investigator (Table 5).

**Table 5 Tab5:** Adverse events severity scale

Severity		
Grade 1	Mild	Transient or mild discomfort (< 48 h); no medical intervention/therapy required
Grade 2	Moderate	Mild to moderate limitation in activity—some assistance may be needed; no or minimal medical intervention/therapy required
Grade 3	Severe	Marked limitation in activity, some assistance usually required; medical intervention/therapy required, hospitalizations possible
Grade 4	Life-threatening	Extreme limitation in activity, significant assistance required; significant medical intervention/therapy required, hospitalization or hospice care probable
Grade 5	Death	

The suspected relationship between study interventions and any AE will be determined by the site investigator. All AEs, including SAEs, will be evaluated as to whether their occurrence was expected or unexpected. An AE will be considered unexpected if the nature, severity, or frequency of the event is not consistent with the known risks associated with the study intervention or with the underlying medical condition (i.e., STEC infection).

The following events and symptoms are routinely expected to occur as part of the natural history of STEC infection, and as such, we a priori determined that they will not be reported as AEs: vomiting, fever, diarrhea, abdominal pain, dehydration, anemia, thrombocytopenia, hospitalization for intravenous rehydration or ongoing oral rehydration therapy, renal insufficiency, HUS, and/or RRT.

